## Abstract

**Background:**

Psychological counseling is perceived as a treatment that could significantly improve older individuals’ psychological and behavioral functioning. There is a dearth of information on the impact of psychological counseling on preserving dignity and facilitating good aging among older people in Singapore.

**Objective:**

The objectives of this study are as follows: (1) to assess advance care planning among older people and their perception of life and health, end of life, and end-of-life care; (2) to explore older people’s accessibility and receptiveness toward counseling; (3) elucidate older people’s perspectives on counseling and its impact on emotional management and decision-making; (4) to assess older people’s competencies in emotional management; and (5) to propose an intervention model for enhancing older people’s well-being and dignity through psychological counseling in Singapore.

**Methods:**

A mixed method study design involving quantitative and qualitative methods will be used. Older individuals receiving some form of preventive, primary, or long-term care in the community through voluntary welfare organizations from the senior activity centers located in eastern Singapore participated in the qualitative phase. Six older individuals from each senior activity center have been enrolled for the interview phase to explore 6 components: the Advanced Care Planning (ACP) booklet, Trait Meta Mood Scale (TMMS), accessibility and receptiveness toward counseling, and emotional management and decision-making. The ACP, an instrument designed to assess advanced care planning among older individuals, and the TMMS, an instrument developed to measure meta-mood experience and emotional management, were used in the quantitative phase among 100 participants. The data will be analyzed thematically using NVivo version 12, whereas descriptive statistics and a 2-tailed, 1-sample *t* test will be conducted in SPSS (version 25; IBM Corp) for empirical data analyses.

**Results:**

The qualitative phase, which involves a semistructured interview, has been completed among 20 older individuals aged 66-86 years. Thematic analysis of the data is still ongoing. Meanwhile, the quantitative phase commenced on March 22, 2022, with 100 participants providing signed informed consent to participate in the study. The study is expected to be completed by March 2023.

**Conclusions:**

The mixed methods study will document the current awareness of ACP, accessibility and receptiveness toward counseling, and the potential use of psychological counseling in enhancing well-being and dignity among older people in Singapore. The research findings will benefit policy makers in their decision-making when attempting to mitigate the potential barriers to seeking counseling assistance among older people.

**International Registered Report Identifier (IRRID):**

DERR1-10.2196/45557

## Introduction

### Overview

The current rising older population in Singapore reflects that one-fourth and half of the population will be older than 65 years by 2030 and 2050, respectively [1]. Previous studies have demonstrated that older people experience diverse aging-related complexities that require counseling intervention: depression, anxiety, grieving, loss of functional health abilities, financial dependence following retirement, social isolation, intergenerational and marital conflicts, and mental and emotional challenges [2,3]. These issues have been increasingly reported among older parents filing for financial maintenance with the tribunal court [4]. Hence, the prevalence of depressed older adults is expected to rise from 19,000 to 50,000 by 2020 [3].

Depression among older people is one of the main causes of suicide in comparison to other age groups globally. Despite implementing relevant policies and high awareness of mental health issues in Singapore to reduce recent suicide rates, the numbers among older adults remain relatively high [5]. For instance, individuals aged 60 years and older accounted for 25%-30% of suicide cases reported in Singapore in 2016, rising to 35.7% in 2017 [5]. Chan [6] also reported that older individuals with extensive depressive symptoms are among the main focus of the Singaporean government.

Recent studies have disclosed the need to accommodate the impacts of demographic shifts on Singapore’s health care eldercare initiatives [7]. The Singapore Ministry of Health provides intermediate and long-term services to address these concerns about the country’s aging population. These policies come in the form of community and residential health care services. While community clinics include hospitals for the chronically ill and nursing homes that are responsible for the provision of residential health care services, center-based health care services are provided by rehabilitation, day care, and psychiatric centers [8].

The Singaporean government has taken diverse approaches to provide better care for older people. For instance, the government is on the verge of increasing the number of nursing home beds to 14,000, accounting for a 50% increase from the report in 2010 [9]. These measures were based on the expected increase in demand for beds as the aging population continues a rising trend [6]. The Ministry of Health has also used smart technologies to facilitate cost-effective eldercare services [10]. Kong and Woods [10] recommended collaborative and contextually sensitive strategies to design and develop smart solutions for older people. Likewise, Ansah et al [11] suggested that resource planners and policy makers proactively review health needs and improve the dignity of the aging population in Singapore.

Despite the availability of previous treatment plans for psychiatric care, counseling is a current treatment approach, especially in recent cases of depression among older people [12]. Psychological counseling is presently perceived as a treatment that could significantly optimize individuals’ psychological and behavioral functioning [12,13]. As most older people spend the remainder of their lives within the community, insights into how residents uphold their sense of dignity within the community are valuable to managing aging stressors. An aging population creates both opportunities and pressures for Singapore’s welfare and health sectors. More importantly, the risk of dignity loss is high among older people during acute hospital care [14].

Dignity is vital to older individuals and their caregivers. However, it remains unclear how older people define dignity or dignified care and how it is influenced by psychological counseling [15]. Past research investigated how older people’s dignity could be safeguarded or enhanced by facilitating individual autonomy [16], providing personalized care, reinstating control, portraying respect, and conducting advocacy and sensitive listening [13]. Identifying older people as individuals and the aspects and values important to them are also fundamentals of care that could potentially conserve their dignity before death [13].

### Why Is It Important to Conduct This Study?

Approximately 30% of the 400 suicide cases reported in Singapore in 2019 involved individuals aged 60 years or older [7]. The number of Singaporeans older than 65 years who lived alone increased from 47,000 (9.7%) in 2016 to 67,600 (11.6%) in 2019 [7]. Previous studies also revealed that older adults with ailments and disabilities are exposed to cumulative suicide risks [17] and depression symptoms [3]. As the implications of aging reflect mental health complexities, aging is affected by several losses that require constant adjustments. Aging-oriented losses involve potential stress factors, specifically for older adults with compromised health conditions. Past studies have also highlighted how ailments and disabilities pose risks to older people and how mitigating factors could substantially reduce diseases and mortality rates among older adults [18].

Given the rising aging population, Singapore’s government health care is unable to accommodate all older people in hospitals and nursing homes. Hence, the Ministry for Social and Family Development developed a policy for older adults to “age in place,” in which they could independently live in their homes and communities. The policy encourages good health by increasing preventive, primary, and long-term care [19]. Additionally, these various types of care offer health and social care needs to support the families of older adults and can be successfully implemented with effective psychological counseling. As physical and cognitive activities represent essential and modifiable protective factors for cognitive decline and dementia, counseling interventions could assist in preventing these issues in older people [3,11].

There is a dearth of information on the effectiveness of counseling older adults in the Singaporean context. However, certain issues have been reported in the literature to impact accessibility and receptivity toward counseling services among the aging population. For instance, the cultural stigmatization associated with psychological counseling services specifically among older people [20,21] makes individuals believe seeking professional counseling is socially unacceptable [22].

Thus, older adults are less inclined and receptive to counselling, even when such assistance is necessary, based on their low awareness of the benefits. Likewise, older adults tend to be deterred by health and disability issues during counseling sessions due to accessibility and receptiveness. These concerns could adversely affect older individuals’ daily functioning and dignity preservation levels.

Counseling could be advantageous for older adults with emotional and psychological issues as a form of antidepressant and for ameliorating various mental disorders for behavioral shifts [23]. Counseling can also assist older adults’ emotional management and decision-making processes by addressing psychological issues. Hence, counseling in emotional management and decision-making processes would enhance the individuals’ sense of dignity in life and aging-oriented transitions. Apart from establishing government-funded counseling services under the family service centers [20], Singapore has also developed social welfare agencies, religious institutions, educational schools, and other governmental institutions that offer counseling services to the general public. Counseling services are also provided by multiple social service agencies and public and private hospitals [21].

Nevertheless, these various counseling services have not been elucidated in the context of Singapore as the impact of psychological counseling in preserving dignity and facilitating good aging among older people remains unknown. In other words, the experience and benefits of the counseling services provided to older citizens are underreported. To fill this research gap, this study aims to propose an intervention model for enhancing older people’s well-being through counseling.

### Research Objectives

The objectives of this study are as follows: (1) to explore older people’s accessibility and receptiveness toward counselling; (2) to assess the improvement of older people’s dignity in emotional management and decision-making processes following psychological counseling; and (3) to propose an intervention model for enhancing older people’s well-being through psychological counseling.

### Research Questions

Due to the paucity of data regarding the impact of counseling services on older adults’ dignity and the aging process, this study aims to answer the following questions:

Do older people in Singapore have counseling access and receptiveness?Do counseling services improve emotional management among older people?Do counseling services improve dignity among older people?Do counseling services affect decision-making processes among older people in Singapore?

## Methods

### Study Design and Study Area

This study uses a mixed method research design by combining quantitative and qualitative approaches to explore the life experiences of Singaporeans older than 60 years and interpret their lived experiences, such as interactions with qualified counselors accredited by the Singapore Association of Counseling and Singapore Association of Social Workers or social workers. Data are gathered using an exploratory sequential mixed methods design, thereby broadening the scope and dimension of the study. Both qualitative and quantitative approaches offer exceptional strengths that will facilitate robust findings in this study [24-26].

The 5 Singaporean estates with a high number of individuals aged 60 years and older [27] were identified. Bedok and Tampines in the eastern part of Singapore have the largest older populations, with 62,750 and 43,700 people, respectively, followed by Hougang in the northeastern part of Singapore with 41,920 older residents and Ang Mo Kio in the northern part of Singapore with 41,390 older residents. Given the high population of older individuals in Bedok and Tampines, older individuals receiving some form of preventive, primary, or long-term care in the community through voluntary welfare organizations (VWOs) have been recruited for this study. Furthermore, a total of 78 senior activity centers (SAC) in Singapore (a VWO with 10 SACs is located in eastern Singapore) were selected for this study.

### Study Population

The study population comprises individuals aged 65 years and older from various parts of Singapore.

### Inclusion and Exclusion Criteria

Textbox 1 shows the inclusion and exclusion criteria for selecting the study participants.

Inclusion and exclusion criteria.
**Inclusion criteria**
Participants must be 65 years of age or older on the first day of selection.Participants must be living in the community.Participants must be interested in the study and receive some form of preventive, primary, or long-term care services.Participants must be willing to attend counseling sessions in emotional management and decision-making processes.

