**Exclusion criteria**
Older individuals who are currently admitted to a nursing home.Older individuals who are mentally incapacitated based on a history of confirmed mental disorder or unable to understand the research protocol when briefed by the researcher.

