### Sample Size Calculation and Sampling Technique

The sample size for the quantitative phase was estimated based on the total population of older people in the study locations, the 95% CI, a precision error of 5%, and estimates from previous related studies on the proportions of participants with satisfactory accessibility and receptiveness levels toward counseling [28]. Specifically, the sample size was estimated by using the formula for analytical and cohort studies presented below:

[figure not shown]

Where

n = sample size

*z*_1–_*_α_*_/2_ = *z* statistic for 95% CI = 1.96

*z*_1-_*_β_* = *z* statistic for 90% power = 1.28

*P*_1_ = Proportion of participants with satisfactory accessibility and receptiveness levels toward counseling in 1 group and

*P*_2_ = Proportion of participants with satisfactory accessibility and receptiveness levels toward counseling in 1 group

*P*_1_ and *P*_2_ were obtained from previous studies reporting the proportions of participants with satisfactory accessibility and receptiveness levels toward counseling [15,28]. The obtained values were substituted into the equation to calculate the required sample size (n). The computed sample size was adjusted for eligibility by assuming that approximately 30% of the participants have access to and are receptive to counseling. Furthermore, a nonresponse rate of 20% was also considered before deciding on the final sample size.

The probability proportionate to size method was used to allocate sample size for each region and part of Singapore to facilitate proportionate distribution of older individuals receiving some form of preventive, primary, or long-term care in the community through VWOs. Thereafter, a simple random sampling technique was used to obtain the required number of participants from each region. Meanwhile, purposive sampling was used in selecting the SACs.

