In terms of the impact of counseling on emotional management and decision-making, diverse views ranging from positive to negative effects may be conveyed by participants since they might have faced challenges in seeking counseling assistance. For instance, a previous study conducted in Tehran, Iran, found that psychological counseling on mental well-being had a positive impact on emotion and self-management ability among older women [57]. Dai et al [58] also performed a meta-analysis of studies conducted among Chinese populations and found that psychologically based therapies were effective in ameliorating depression symptoms among older people. The contents of the ACP instrument used in this study entailed pertinent topics on mental health, the selection of treatment goals (comfort-focused vs full treatment), available care options in the community, and available care options during end of life, which might have a positive effect on emotional management and decision-making. However, difficulties in assessing counseling services or challenges are faced during the counseling process.

The fourth objective of this study emphasized participants’ competencies in emotional management after counseling assistance. This objective will entail both a semistructured interview and a quantitative analysis by using the TMMS, which focuses on participants’ attention (perceived attention paid to personal emotional conditions), clarity (perceived understanding of personal emotional conditions), and repair (perceived ability to regulate personal emotional conditions). The TMMS is one of the most commonly used self-administered measurements for perceived emotional competence in older people [29]. It provides the opportunity to bridge current empirical gaps on emotions and to elucidate developmental trajectories throughout a person’s life span. Based on the alignment between the ACP contents and items in the TMMS, as well as findings from previous local studies on the impact of counseling [20], we expect older people’s competencies in emotional management and decision-making to improve after seeking counseling assistance. Results from this study may assist policymakers in deploying strategies to promote mood repair and emotional management in the Singaporean aging population to improve their receptiveness toward counseling interventions.

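### Entry does not require that anyone has had counseling, yet parts of the article read whole-sample results as improvement or competence after counseling, while its own objective list does not

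*Protocol article*

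**What the plan says.** **Who may enter.** Textbox 1 asks for age 65 or older, community living, interest in the study, and that participants "receive some form of preventive, primary, or long-term care services". Its one criterion on counseling is "Participants must be willing to attend counseling sessions in emotional management and decision-making processes". The exclusions are nursing home residence ("Older individuals who are currently admitted to a nursing home") and mental incapacity or inability to understand the protocol. Neither list mentions past or current counseling.

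**What is measured.** The ACP and TMMS instruments and a structured questionnaire are administered to 100 participants. Strengths and Limitations calls the design cross-sectional. Data Analysis gives descriptive statistics and a one-sample t test or Wilcoxon signed rank test, and names no grouping by counseling history.

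**How the results are to be read.** The article gives two accounts.
- Research Objectives sets out to assess improvement in "dignity in emotional management and decision-making processes following psychological counseling", and Research Questions asks whether counseling services improve emotional management and dignity. Study Design and Study Area aims to "interpret their lived experiences, such as interactions with qualified counselors accredited by the Singapore Association of Counseling". Expected Findings frames objective 4 as "competencies in emotional management after counseling assistance" and adds: "This objective will entail both a semistructured interview and a quantitative analysis by using the TMMS". It expects competencies to improve once counseling has been sought.
- The Abstract's objective list and Table 1 state objective 4 simply as assessing competencies in emotional management. Table 1 ticks only the quantitative column for it.

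**The concern.** A statement about people after counseling needs people who have been counseled. Under Textbox 1, someone who has never met a counselor is fully eligible. That person's TMMS score is averaged with the score of someone who has had many sessions, and their answers on what counseling does are expectations rather than experience.

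This is separate from the lack of a baseline or comparator. Even a purely descriptive mean labeled as after counseling would be taken over people to whom the label need not apply. The proposed intervention model draws on these results, so expectation could be presented as experience.

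**Working it through.** **Step 1: is prior counseling implied by any entry rule?**
- Counseling criterion: willingness to attend, which says nothing about past attendance.
- Care criterion: preventive, primary or long-term care. Counseling is not named.
- Exclusions: none concerns counseling history.
- Study-delivered sessions between entry and measurement: none described.

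A never-counseled person is therefore eligible, and is measured once without having been counseled by the study.

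**Step 2: do the statements of objective 4 agree?**

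| Place | Counseling condition | Data source |
|---|---|---|
| Abstract, Objective | none | not stated |
| Table 1 | none | quantitative only |
| Expected Findings | after counseling | interview and TMMS |

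They differ on both counts. Research Objectives has its own three-item list, whose second item is about improvement following counseling. Only the Abstract and Table 1 wording can be answered in the population that Textbox 1 admits.

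**Step 3: is there a figure for the share ever counseled?** No. The nearest is in Sample Size Calculation and Sampling Technique, where n was adjusted for eligibility by "assuming that approximately 30% of the participants have access to and are receptive to counseling". That concerns access and receptiveness, not receipt, so it cannot be used as f. There is no exposure figure in the article to reproduce.

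**Step 4: what mixing does to the mean, for any f.** Let μ₀ be the mean TMMS subscale score of never-counseled participants, μ₀ + D that of counseled participants, and f the counseled share.
- Pooled mean = (1 − f)μ₀ + f(μ₀ + D) = μ₀ + fD.
- Shortfall from the counseled mean = (μ₀ + D) − (μ₀ + fD) = (1 − f)D.

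The values of f below are assumptions, chosen only to show the range. N = 100 is from the Results. The last column is the standard error of the counseled-only mean relative to that of all 100, which is 1/√f if the SD is the same in both groups.

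| f (assumed) | Counseled, of 100 | Pooled shift | Shortfall | SE ratio |
|---|---|---|---|---|
| 0.2 | 20 | 0.2D | 0.8D | 2.24 |
| 0.5 | 50 | 0.5D | 0.5D | 1.41 |
| 0.8 | 80 | 0.8D | 0.2D | 1.12 |

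**Step 5: precision of a comparison by counseling history.** With common SD s, the standard error of the difference is s√[1/(100f) + 1/(100(1 − f))].
- f = 0.5: s√(1/50 + 1/50) = 0.20s, a 95% half-width of 1.96 × 0.20s = 0.39s.
- f = 0.2 or 0.8: s√(1/20 + 1/80) = 0.25s, a half-width of 0.49s.

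**The case against.** Several points on the other side have force.

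- **The article already states objective 4 correctly in two places.** This stands. The reading as a state after counseling is tied to the TMMS only in Expected Findings, so for that objective the defect is one of inconsistency. Research Objectives and Research Questions do, however, speak of improvement from counseling.
- **Admitting never-counseled people suits other objectives.** This also stands. Accessibility, receptiveness and barriers cannot be studied only in people who have used counseling, and anyone can hold a view of it. The entry rule is therefore not wrong in itself. What fails is the later description of everyone admitted.
- **Counseling history may have been collected.** It may have been. The article prints neither the structured questionnaire nor the background items, and an analysis by history could sit in a plan not shown. Its absence from a condensed article is not a finding. The Management section refers to participants' counseling at the centers, which suggests that some have had it, but this is not an entry rule.
- **Strengths and Limitations rules out causal inference.** That deals with confounding. It does not tell the reader that respondents may never have been counseled.

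A reader might go further and infer from the 30% that about 70 of the 100 surveyed, or most of the sample, had no counseling. The article does not support this. The 30% is an eligibility adjustment about access and receptiveness. It is not an upper bound on ever having been counseled, since someone counseled in the past may no longer be receptive. It also transfers poorly to enrolled participants, all of whom had to be willing to attend.

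**Conclusion.** The concern holds as a mismatch between whom the article admits and how parts of it read the results. Textbox 1 allows never-counseled participants, and no study counseling is described. Research Objectives, Research Questions and Expected Findings nevertheless speak of improvement or competence after counseling, against the Abstract and Table 1.

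The distortion is f × D in place of D, with neither quantity given. It disappears if everyone had been counseled and grows as f falls. No claim is made that most participants were unexposed or that history went unrecorded. The conclusion rests on the printed entry criteria and objectives. The formula adds only the assumption that counseled and never-counseled people may differ in mean score.

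**What to change.** 1. **Reconcile the wording.** Bring Research Objectives, Research Questions and Expected Findings into line with the Abstract and Table 1. State objective 4 as emotional competence of the sampled senior activity center users, and remove the after-counseling and improvement language from the whole-sample TMMS result. Settle whether objective 4 uses the interview as well, since Table 1 and Expected Findings disagree.
2. **Use counseling history where it exists.** If it is already in the collected data, or can be obtained from center records within the existing consent and ethics approval, report the number ever counseled. Give TMMS and impact responses separately for ever- and never-counseled participants. Limit impact statements to the former and label the latter's views as expectations.
3. **If history cannot be recovered,** say so in the limitations and make no statement about states after counseling.

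Data collection closed on May 10, 2022, so new questionnaire items or a changed entry criterion are no longer options. Step 1 costs only editing. Step 2 costs some data work, and a record look-up needs a check first, because the article's consent and confidentiality text does not describe one. The counseled subgroup will be smaller and its estimates less precise, and a comparison by history is at best accurate to about 0.4 SD either way, as worked above.

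### Willingness to attend counseling is an entry criterion, so the study cannot show how receptive older people in Singapore are to counseling

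*Protocol article*

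**What the plan says.** The relevant statements in the protocol article are these.

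- **Inclusion criteria (Textbox 1).** "Participants must be willing to attend counseling sessions in emotional management and decision-making processes". Also: "Participants must be interested in the study and receive some form of preventive, primary, or long-term care services". No separate criteria are given for the interview phase and the survey phase.
- **Study Design and Study Area; Sample Size Calculation and Sampling Technique.** Participants come through voluntary welfare organizations and purposively selected senior activity centers.
- **Research Objectives.** One aim is "to explore older people’s accessibility and receptiveness toward counselling". The Abstract lists the same aim.
- **Research Questions.** "Do older people in Singapore have counseling access and receptiveness".
- **Study Population.** "The study population comprises individuals aged 65 years and older from various parts of Singapore".
- **Sample Size Calculation and Sampling Technique.** The planning parameters are each defined as "Proportion of participants with satisfactory accessibility and receptiveness levels toward counseling in 1 group", with no values given. The result was then "adjusted for eligibility by assuming that approximately 30% of the participants have access to and are receptive to counseling".
- **Table 1 and Expected Findings.** Accessibility and receptiveness are assigned to the qualitative component only.
- **Strengths and Limitations.** The criteria are said, in general terms, to have possibly left out informative people. Neither receptiveness nor a direction of bias is named.

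**The concern.** Being willing to go to counseling is close to what receptiveness means. If only willing people may enrol, a conclusion that participants are receptive partly restates the eligibility rule.

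The protocol's own background (Why Is It Important to Conduct This Study?) describes older adults as less receptive to counseling even when they need it, citing stigma and low awareness of its benefits. People held back in that way are the ones the criterion turns away.

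The Abstract's conclusions and the closing Conclusion nevertheless promise policy makers guidance on removing barriers and raising receptiveness among older people generally. That guidance would rest on a group from which the least receptive were excluded. A larger sample recruited under the same rule would not help.

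**Working it through.** **1. Objective against entry rule.**

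| Attribute | Asked about in | Fixed at entry? |
|---|---|---|
| Receptiveness to counseling | Research Objectives, Research Questions | Largely yes: willingness to attend is mandatory |
| Access to counseling | Same | No: the care criterion covers other kinds of care, and someone in primary care may have no counselor within reach |
| Barriers that remove willingness (stigma, low awareness) | Expected Findings, Abstract conclusions | Largely unobservable: people deterred in this way do not qualify |
| Practical barriers (cost, health, disability) | Same | No: a willing person can still face and report them |

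**2. Where the selection carries forward.** Under Instrument Development and Data Analysis, interview themes feed the structured questionnaire. Themes held only by unwilling people cannot enter it.

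**3. Direction.** Let π be the receptive share in the target population, s the share of receptive people who pass the willingness screen, and f the share of non-receptive people who pass it. Then

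receptive share among enrolled = πs / (πs + (1 − π)f).

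This exceeds π whenever f < s, which is what a willingness criterion is built to produce. The documents give none of the three quantities. With s = 1 and the other values assumed purely for illustration:

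| π (assumed) | f = 0 | f = 0.10 | f = 0.25 | f = 0.50 | f = 1 |
|---|---|---|---|---|---|
| 0.20 | 100% | 71% | 50% | 33% | 20% |
| 0.30 | 100% | 81% | 63% | 46% | 30% |
| 0.40 | 100% | 87% | 73% | 57% | 40% |

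For example, π = 0.30 and f = 0.10 give 0.30 / (0.30 + 0.70 × 0.10) = 0.30 / 0.37 = 81%. The table shows direction only. The bias disappears only when the criterion excludes nobody (f = 1 when s = 1).

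**4. Why the 30% does not give a size.** Read it, as an assumption, as the population share with both access and receptiveness, and call the receptive share R, so R is at least 0.30. If the screen admits only receptive people:

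- Receptiveness alone rises from R to 100%, a shift of 1 − R. That is 70 points if R = 0.30, 50 points if R = 0.50 and none if R = 1.
- The joint figure rises from 30% to 0.30 / R. That is 100% if R = 0.30, 60% if R = 0.50 and 30% if R = 1. Willingness does not confer access.

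R is not stated. The sentence also speaks of participants rather than older people. Taken literally, it says that most participants lack access, receptiveness or both, which fits poorly with calling it an eligibility adjustment.

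**5. The sample-size sentence.** The same attribute is both the planning parameter (the two proportions) and the factor used to adjust for eligibility. An attribute under study cannot also be the eligibility rate without making the question circular. The enrolled 100 cannot be reproduced, because the two proportions are not given; this does not affect the point.

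**The case against.** The other side has real force on several matters.

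- **No planned proportion.** Table 1 and Expected Findings treat this objective as qualitative, and the analysis section names no receptiveness percentage. This stands. A reader might infer a 70-point upward bias (100% − 30%), but no planned estimate would carry it, and the 30% is a joint figure of uncertain denominator.
- **Access is not screened.** This stands for Textbox 1. A reader might infer that accessibility is selected for as well, but the care criterion does not concern counseling. Only the eligibility sentence in the sample-size section points that way, and it is ambiguous.
- **Willing people still meet barriers.** This stands. Expected Findings anticipates participants who had difficulty seeking help. It would be wrong to infer that nobody facing a barrier can enrol.
- **The criterion may serve other aims.** The article describes no counseling delivered by the study, so a reader might infer that the criterion is pointless. But other objectives concern the perceived impact of counseling and experience with counselors, and people open to counseling are a plausible source for those.
- **The limitation is disclosed.** Only in part. The general remark in Strengths and Limitations does not tell a reader that unwilling people were excluded or which way this pushes the result, and the research question and conclusions are not narrowed.

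A qualitative design does not remove the core problem. Interviews confined to willing people cannot describe unwillingness at first hand, and the research question is still put to older people in Singapore as a whole.

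**Conclusion.** The point holds for receptiveness and for barriers that act by removing willingness. On these, the study can speak only for service-connected older people already prepared to attend counseling. It does not hold for counseling access or for practical barriers, which can vary among those enrolled, although there too the sample is limited to people reached through care services.

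The direction is toward overstated receptiveness and understated reluctance. This assumes that the willingness criterion was applied as written and that less receptive people pass it less often. No size can be given from the documents, and none should be quoted.

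The consequence is a mismatch between the population studied and the population named in the research question, the Abstract's conclusions and the Conclusion.

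**What to change.** The Results section reports that data collection closed on May 10, 2022, so removing the criterion would change nothing in these data. The changes are:

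1. **Population.** For the receptiveness and barrier objectives, the corresponding research question, and the policy statements in the Abstract and Conclusion, name the population as older people in contact with services and already willing to attend counseling.
2. **Limitations.** State in Strengths and Limitations that people unwilling to attend counseling were excluded, that reluctance-based barriers are therefore largely unobserved, and that receptiveness is likely overstated.
3. **Recruitment counts.** Where records allow, report how many were excluded or declined because they were unwilling to attend counseling, separately from those who declined the study itself. If the records cannot separate the two, say so. This describes the selection; it does not create a new receptiveness estimate.
4. **Sample size.** Remove or correct the 30% eligibility adjustment, since access and receptiveness are the attribute under study and the planning parameter. If the sentence meant something else, state what the 30% is a share of.

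The cost is rewording, plus a count if a recruitment log exists (none is described). The downside is a narrower claim.
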